During the intervention, each meal is planned by a clinical nutritionist. We provide lunch daily to each participant during the course of the intervention. The lunch accounts for 40% of the total daily energy intake. The breakfast and dinner each account for 30% of the total daily energy intake. The proportion of macronutrients are planned as 30-40% carbohydrate with < 5% sucrose and with 18-20% as fiber, 40% fat (SAFA 10%, MUFA 15-20%, PUFA 10%) and 20% protein. The lunch will be prepared under the guidance of a clinical nutritionist at the Student Restaurant of Shanghai University of Sport. Each meal will contain three to four dishes of foods commonly eaten by Chinese families in Shanghai. A trained study staff member will weigh each item for each specific person according to the dietary plan and the cooked dishes will be put into a named lunch box for each participant. The lunch box will be then delivered to the study district office where the study subjects are gathered and the eating will be monitored. If the participants don’t have time to come to the lunch, the lunch box will be delivered to their home and we will ask the participants to take it as their dinner.

The subjects will cook their breakfast and dinner by themselves and eat the proportion following the nutritionist advices. They will take the pictures of each meal by an iPhone provided by the research. A researcher will upload the pictures weekly to our data management server for further evaluation.

3. Exercise + diet group:

The AEx + LCh group will perform the same exercise program and follow the same diet program as abovementioned for AEx and LCh groups.

4. Control and reference groups:

The control and reference groups will be advised to maintain their level of physical activity and habitual eating during the intervention. After intervention, we will provide to the control group an opportunity to participate in our planned exercise and diet intervention for 3 months.

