#### Concomitant adherences and procedures

During the intervention, an exercise instructor will ensure that each individual has the right starting level and will follow their progress during the entire trial. We will organize the participants into groups according to their time and places of residence. Exercising together as a team will increase their compliance. A group leader of each 10 subjects will be selected by participants to assist the instructor to ensure a high participation rate. The exercise instructor will be with the subjects at least three times a week during the intervention. Group feedback meetings will be arranged every 3 months during the trial by an exercise specialist.

To ensure good compliance in diet intervention, we provide a mobile phone to the subjects to allow them to take photographs of their breakfast and dinner daily during the study. The photos are downloaded by a researcher weekly. The study nutritionist analyses dietary composition from the uploaded photos and gives feedback to each participant monthly. In addition, food diary information is also collected at the 3-month time point in order to give more dietary suggestions to the subjects. A clinical nutritionist will hold nutritional education meetings three times for the diet and AEx + LCh groups during the intervention period.

For the control and reference groups, we will keep in contact with them via phone call monthly and questionnaire to check on their physical condition and lifestyle at 3 and 6 months follow-up during the intervention.

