### Statistical methods

All data collected by questionnaires will be entered into database management software (Filemaker Pro version 10, FileMaker Inc. Santa Clara, CA, USA), double checked by independent researchers, and exported to PASW statistics version 20 (IBM Corporation, USA). If data is not normally distributed, their natural logarithms will be used for further analysis. Descriptive statistics will be used to present the background and anthropometric data at the baseline and follow-up assessments as mean and 95% confidence interval (CI) unless otherwise stated.

An intention-to-treat (ITT) analysis will be performed to compare the AEx, LCh and AEx + LCh groups to Con group. The effects of the interventions will be assessed using analysis of variance (ANCOVA) for repeated measures (treatment group × time) and baseline difference as a covariate. If the significance of the group by time interaction is p < 0.05, the effect will be localized utilizing Bonferroni for multiple comparisons. The level of statistical significance chosen for the contrasts will be p < 0.05. In addition to the ITT analysis, efficacy or active treatment analysis will be done when the compliance of the participation of the intervention is ≥60% of the whole trial and for <60% not more than 3 months continuously [ANCOVA for repeated measures (treatment group × time) and baseline difference as a covariate.] The percentage differences (0–6month) will be calculated from duration between baseline and end point measurements for each individual. The comparison of percentage changes in different groups will be performed using ANCOVA (two factor interactions: compliance/noncompliance × treatment group) controlled for the baseline value using Bonferroni for multiple comparisons. If the significance of the overall group difference is p < 0.05, then the effect will be localized by contrast to the Con group. When the 95% CI does not include zero, the difference is regarded as statistically significant at α = 0.05.

Linear Pearson’s correlation, partial correlation, Kendall Tau’s, and bivariate, logistic, and multivariate regression analysis will be used for analysing relationships. In addition, systems biology approaches will be used to develop models which integrate the different types of data and the high-throughput data measured in terms of gut microbiota composition and fecal SCFAs content, as well as LPSs and inflammation.

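### The percentage-change ANCOVA crosses treatment with a compliance factor that the control group cannot fill, and the ≥60% efficacy contrast with Con is not a randomised comparison

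*Protocol article*

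**What the plan says.** All the analysis rules are in the protocol article, Statistical methods. In order:

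- An ITT repeated-measures ANCOVA compares AEx, LCh and AEx + LCh with Con.
- In addition to that, "efficacy or active treatment analysis will be done when the compliance of the participation of the intervention is" at or above a threshold. The full criterion is "compliance of the participation of the intervention is ≥60% of the whole trial and for <60% not more than 3 months continuously".
- For 0–6 month percentage change: "The comparison of percentage changes in different groups will be performed using ANCOVA (two factor interactions: compliance/noncompliance", crossed with treatment group and adjusted for baseline. If the overall group difference has p < 0.05, each group is contrasted with Con.

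Three statements elsewhere describe what Con does in those six months:

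- Interventions, item 4: "The control and reference groups will be advised to maintain their level of physical activity and habitual eating during the intervention".
- Same item: "After intervention, we will provide to the control group an opportunity to participate in our planned exercise and diet intervention for 3 months".
- Concomitant adherences and procedures: "For the control and reference groups, we will keep in contact with them via phone call monthly and questionnaire".

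The article gives no compliance criterion for Con.

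**The concern.** A factor can be crossed with treatment only if every arm can show every level of it. Compliance here means taking part in a programme, and Con has none before month 6. The stated model therefore lacks a cell, and the missing cell belongs to the arm that every contrast uses as its reference. The percentage-change comparison has no stated version by randomised arm alone that could stand in its place.

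The ≥60% efficacy analysis raises a second, separate issue. Adherence is observed after randomisation. If people who adhere would have done better anyway, setting them against Con credits the programme with a difference in the people. The risk is that a percentage reduction or an efficacy result is reported as a treatment effect when randomisation does not support it.

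**Working it through.** **A. Can the stated model be fitted?** This needs only the document. There are 4 groups and 2 compliance levels. The parameters are 1 intercept + 3 group + 1 compliance + 3 interaction = 8. The baseline covariate adds a column but does not alter the argument.

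| How Con is recorded | Cells filled | Rank | Consequence |
|---|---|---|---|
| Both levels (needs a rule the article lacks) | 8 | 8 | Model can be fitted |
| All compliant, or all non-compliant | 7 | 7 | Interaction df 7 − 1 − 3 − 1 = 2 instead of 3; one parameter not estimable |
| Missing | 6 | 6 | Con leaves the model; no contrast with Con |

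In the 7-cell case a Con mean averaged over both compliance levels is not estimable. The overall group test that gates the contrasts then depends on how the software handles the empty cell.

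**B. Does the coding of Con matter?** Illustration with assumed values: a true benefit of 0.50 SD for everyone in an active arm, a correlation r between latent adherence and outcome, and a complier share q. With c the normal cut-off for q and φ the normal density, compliers differ from the arm mean by r·φ(c)/q and non-compliers by −r·φ(c)/(1 − q). φ(c) is 0.280 at q = 0.8 and 0.386 at q = 0.6.

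| r | q | Shift, compliers | Shift, non-compliers |
|---|---|---|---|
| 0.2 | 0.8 | 0.2 × 0.280/0.8 = 0.07 | −0.2 × 0.280/0.2 = −0.28 |
| 0.3 | 0.8 | 0.3 × 0.280/0.8 = 0.11 | −0.3 × 0.280/0.2 = −0.42 |
| 0.2 | 0.6 | 0.2 × 0.386/0.6 = 0.13 | −0.2 × 0.386/0.4 = −0.19 |
| 0.3 | 0.6 | 0.3 × 0.386/0.6 = 0.19 | −0.3 × 0.386/0.4 = −0.29 |

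If Con is coded compliant, the same-level contrast estimates 0.57–0.69 SD. If Con is coded non-compliant, it estimates 0.08–0.31 SD. Comparing all randomised subjects by arm recovers 0.50.

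**C. Efficacy subset under no true effect.** Inputs: 50 per group and 15% drop-out (Sample size estimation) give 50 × 0.85 = 42.5, taken as 42. r and q are assumed as above. All of Con is assumed to be kept. SE = √(1/(42q) + 1/42).

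- r = 0.2, q = 0.8: bias 0.07, SE √(1/33.6 + 1/42) = 0.231, shift in z = 0.30. Rejection is 6.1% at two-sided 5%.
- r = 0.3, q = 0.6: bias 0.19, SE √(1/25.2 + 1/42) = 0.252, shift in z = 0.77. Rejection is 12.0%.
- At 0.05/3 = 0.0167 (three contrasts with Con) the same inputs give 2.2% and 5.3%.

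As a cross-check, a simulation with 50 per arm and 4,000 runs per setting covered complier shares of 60–85% and correlations of 0.2–0.5. The bias was 0.05–0.32 SD and rejection at 5% was about 6–30%. At zero correlation rejection stayed near 5%.

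**The case against.** The strongest reply is that the plan already has a sound analysis. The ITT repeated-measures ANCOVA comes first, uses randomised groups only, and is untouched by any of this. That stands. A reader might infer that the trial's main or headline effect comes from a non-randomised model. The document does not support this: it gives the percentage-change comparison no such rank, and it calls the efficacy analysis an addition to ITT.

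A reader might also attach the 0.07–0.19 SD bias to the compliance × treatment model. That does not follow. That model keeps compliers and non-compliers as separate levels, whereas the bias was worked out for compliers alone against Con.

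Con could be scored on keeping its habits, since all groups receive a diary and a step counter (Measurements procedures, Randomization visit). That is possible, but it would be a different quantity from participation in an intervention, and the article does not define it. It is also fair to say that keeping all of Con in the efficacy set is an inference. The article does not say how Con enters. Read literally, Con has no participation before month 6 and would be left out.

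Leaving such coding to an analysis plan would be a good answer if the article were silent. Here it states a model and a reference contrast that do not fit together.

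The percentage scale might seem a further defect, because the plan's remedy for non-normal data, "If data is not normally distributed, their natural logarithms will be used for further analysis", cannot be applied to negative percentage changes. But the rule does apply to liver fat itself, and any gain from the log scale is a modest one in efficiency that rests on assumed distributions.

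**Conclusion.** The point holds for two secondary parts of the plan. First, the percentage-change ANCOVA cannot deliver its contrast with Con as written. This follows from the document alone: rank 7 of 8 with Con at one level, or no Con at all if its compliance is missing. Second, the ≥60% efficacy contrast is not protected by randomisation. Its possible bias, about 0.07–0.19 SD in favour of treatment, and its null rejection of 6–12% at nominal 5% (2–5% at 0.0167) rest on assumed correlations of 0.2–0.3, assumed complier shares of 60–80% and the assumption that all controls are kept. If adherence is unrelated to outcome, there is no bias. The ITT comparison is not in question.

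**What to change.** 1. Remove the compliance factor from the percentage-change comparison. Compare all randomised subjects by arm against Con, adjusted for baseline. For liver fat this can be an ANCOVA of log(HFC) at month 6 on log(baseline HFC) and arm, reported as 100 × (exp(b) − 1) with its confidence interval.
2. Examine compliance only within AEx, LCh and AEx + LCh. Label that analysis and the ≥60% efficacy subset exploratory, with no confirmatory p-value against Con.
3. Present any complier-average estimate that uses randomised arm as instrument as a sensitivity analysis only, and state its assumption of no effect below 60% attendance. The assumption is strained because partial attenders may benefit. For example, if 70% pass the threshold and the rest gain half the effect, the estimate is (0.70 + 0.30 × 0.5)/0.70 = 1.21 times the true complier effect.

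The cost is a change of wording and little extra analysis. The downside is that the efficacy contrast can no longer support a confirmatory claim.

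### Liver fat has two gated tests against control, one on the measured or log value and one on individual percentage change, and the plan does not say which decides.

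*Protocol article*

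**What the plan says.** All of this is in the protocol article's Statistical methods section unless another section is named.

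- **First route.** "An intention-to-treat (ITT) analysis will be performed to compare the AEx, LCh and AEx + LCh groups to Con group". The model is given next: "The effects of the interventions will be assessed using analysis of variance (ANCOVA) for repeated measures (treatment group × time) and baseline difference as a covariate". Its gate is: "If the significance of the group by time interaction is p < 0.05, the effect will be localized utilizing Bonferroni for multiple comparisons". Its scale depends on the data: "If data is not normally distributed, their natural logarithms will be used for further analysis".
- **Efficacy set.** "In addition to the ITT analysis, efficacy or active treatment analysis will be done", using the same model in participants with enough compliance.
- **Second route.** "The percentage differences (0–6month) will be calculated from duration between baseline and end point measurements for each individual". Then: "The comparison of percentage changes in different groups will be performed using ANCOVA (two factor interactions: compliance/noncompliance × treatment group"), controlled for baseline and with Bonferroni. Its gate is: "If the significance of the overall group difference is p < 0.05, then the effect will be localized by contrast to the Con group".

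The Primary outcomes section schedules liver fat at baseline and 6 months. The Sample size estimation section powers a comparison of mean liver fat but names no scale.

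**The concern.** Each route is a complete decision procedure: an outcome, a model, a gate at 0.05 and contrasts against Con. For liver fat at 0 and 6 months, both address the same change. They do not estimate the same quantity. A raw change is driven mainly by people who start with high liver fat. A percentage change weights everyone equally and is skewed.

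The percentage-change analysis is not called secondary, supportive or descriptive, and having its own gate and contrasts makes it inferential. If the two routes differ, the plan allows the trial to be reported as positive or negative on a primary outcome, and the choice can be made after the results are seen.

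**Working it through.** **1. Inputs from the protocol.** There are four randomised arms of 50 with 15% drop-out, so 50 × 0.85 = 42.5, taken as 42 per arm. Entry requires liver fat above 5%. The sample size section gives 34 per group for 85% power at 0.05, with Bonferroni for 10 comparisons.

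**2. The plan's own figure.** From n = 2(z₁₋α/₂ + z₀.₈₅)²/d², the implied standardised difference is d = (z₁₋α/₂ + z₀.₈₅) × √(2/34).
- α = 0.05: (1.960 + 1.036) × 0.2425 = 0.73.
- α = 0.05/10 = 0.005: (2.807 + 1.036) × 0.2425 = 0.93.

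The section gives no difference, SD or scale, so 34 can be neither confirmed nor refuted. It does not show which scale was meant to decide.

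**3. Why both routes ask about the same change.** With only baseline and month 6, and baseline as covariate, the group × time test reduces to a comparison of the four arms at month 6 given baseline:
- Route 1: Y₆ (or log Y₆) = arm + baseline.
- Route 2: 100(Y₆ − Y₀)/Y₀ = arm + baseline, plus the compliance × arm term.

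On the log scale, an arm effect β back-transforms to a percentage difference from Con of 100(e^β − 1). For example, β = −0.20 gives −18% and β = −0.30 gives −26%.

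**4. Simulation.** The following inputs are assumptions and are not in the protocol:
- baseline liver fat lognormal, median 10–11%, log SD 0.4–0.6, truncated at 5%;
- multiplicative change with log SD 0.30–0.50;
- 42 per arm (50 in some settings);
- AEx + LCh effects of −0.20 to −0.30 for the contrast figures.

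Each route has an overall F gate at 0.05, then three contrasts with Con at 0.05/3. The compliance term is left out.

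| Quantity | Result |
|---|---|
| No effect: each gate alone | about 5% |
| No effect: either gate opens | about 5–7% |
| Same, if the tests were independent: 1 − 0.95² | 9.75% |
| No effect: a gated, Bonferroni-adjusted claim on either route | about 3–4% |
| No effect: the same claim on ITT alone | about 2.5–3% |
| Intermediate power: log ITT and percentage change disagree on AEx + LCh vs Con | about 7–10% |
| Same, raw ITT | about 13–22% |
| High power: log ITT and percentage change disagree | about 1% |

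With half-size effects in the single-intervention arms, the two intermediate-power rows become 7–11% (log) and 10–21% (raw). At log SD 0.6, change SD 0.45 and effect −0.30, power is 0.48 for raw ITT, 0.62–0.65 for percentage change and 0.68–0.70 for log ITT.

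**5. A different shape of effect.** Suppose treatment removes a fixed number of points instead (1.5, 1.5 and 2.5 points in the three active arms, change SD 4). The overall gates then have power 0.65 (absolute), 0.60 (percentage) and 0.47 (log), and the log and percentage gates disagree in 19% of trials. Which scale is more favourable therefore depends on a pattern not known in advance.

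**The case against.** **ITT is implicitly primary.** It comes first and carries the stated purpose of comparing the three active groups with Con, and the efficacy analysis is introduced as additional. This stands as a hint. It ranks the ITT population over the efficacy set but says nothing about measured or log value versus percentage change.

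**The percentage-change test belongs to the efficacy analysis.** Its compliance × group term allows that reading, and it means the test is not purely the first one on another scale. The text does not say so, however, and a factor with a noncompliant level implies that noncompliers are included. The omitted term also means that the simulation sizes a simpler model than the planned one.

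**The raw-scale figures would rarely apply.** This largely stands. For the skewed data assumed here, a normality test rejects in essentially every trial, so the plan's own rule would lead to logs. The 7–10% figure is the relevant one, and 13–22% applies only if raw values are kept.

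**A reader might infer more than the text supports:**
- *That the false-positive rate nearly doubles.* Counting the efficacy set as a third gate gives 7.5–9.6%, but the protocol presents that analysis as an addition to ITT. The two scales are also highly correlated.
- *That the percentage-change route has a competing significance rule.* A 95% interval excluding zero is the same 0.05 criterion already set for the ITT contrasts.
- *That every outcome is affected alike.* Microbiota is also measured at 3 months, and the follow-up visits add month-12 imaging. A group × time test over more visits is not the same as a 0–6 month change.

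**Ranking is work for an analysis plan.** An analysis plan not shown here may do it. The point concerns what the article itself fixes: two gated tests that can give opposite answers on a primary outcome.

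**Conclusion.** The point holds for liver fat at 0–6 months and is worth correcting. That two unranked gated tests exist follows from the text alone. Their size rests on the assumed baseline distribution, change SD and effects, and on leaving out the compliance term.

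On those inputs the type I cost is minor, and a Bonferroni-adjusted claim stays under 5%. What matters is the undefined verdict in borderline results: roughly one trial in ten to fourteen on the log scale at intermediate power, and about one in a hundred when power is high.

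**What to change.** In Statistical methods, state that the ITT baseline-adjusted ANCOVA at month 6 is the decisive analysis for liver fat. Fix its scale in advance as log(month 6) adjusted for log(baseline), in place of the data-dependent choice. The arm effect still reads as a percentage difference from Con. Label the individual percentage-change and efficacy-set analyses supportive, so that their gates cannot by themselves support a claim of effect. Neither needs to be deleted.

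The change is wording only, with no added participants, visits or data. There are two costs. A result significant only on a supportive analysis can no longer be claimed as the trial's finding. If the true effect is a fixed number of points, the log scale gives up some power, as step 5 of the working shows.

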#### Sample size estimation

The sample size calculation (drawing on previous literature) with an estimate of how many participants will be needed for the primary outcome to be statistically, clinically and/or politically significant. For the specific primary outcome of liver fat and microbiota, based on our plot study, 34 subjects in each group would have 85% power for mean comparison between the randomized groups for the liver fat. We set the significance level at 0.05 and allowed for 10 mean comparisons with the Bonferroni correction between the groups. Taking into account multi-variable comparisons in the analysis, we increase our simple size to 50 in each group. We also taking into account the compliance and drop-out (15%), thus the total number of subjects was estimated to meet each specific aim.

In addition, typical projection-based methods used to analyze whole-genome data, such as Principal Component or Partial Least Squares Regression, do not have statistical inference methods. Thus, the corresponding methods for sample size estimation are data-driven methods involving latent variables. However, the large dimension and the time series nature of our datasets provide a good opportunity for inferring associations between different measurements. By using a systems biological approach we can develop models based on path analysis, which comprehensively integrate data for analysis. With such models we will be able to reveal the relationships between different variables.

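### The 10 Bonferroni comparisons used for sizing match no planned family of randomised-arm contrasts, and the 95% CI rule for percentage change does not say whether its intervals are Bonferroni-adjusted

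*Protocol article*

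**What the plan says.** Sample size estimation states that "34 subjects in each group would have 85% power for mean comparison between the randomized groups for the liver fat" and continues: "We set the significance level at 0.05 and allowed for 10 mean comparisons with the Bonferroni correction between the groups". The effect behind this is attributed to a pilot study ("based on our plot study"), but neither a difference nor an SD is given. The group size is then raised: "Taking into account multi-variable comparisons in the analysis, we increase our simple size to 50 in each group". A 15% allowance for compliance and drop-out is also mentioned.

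Statistical methods defines the main comparison: "An intention-to-treat (ITT) analysis will be performed to compare the AEx, LCh and AEx + LCh groups to Con group". For the repeated-measures ANCOVA, a group-by-time interaction at p < 0.05 opens the way to Bonferroni comparisons, and contrasts are judged at p < 0.05. For the 0–6 month percentage changes, the section names ANCOVA with Bonferroni, requires an overall group difference at p < 0.05, and then localises the effect by contrast with control. The paragraph closes with "When the 95% CI does not include zero, the difference is regarded as statistically significant", and sets α at 0.05. The section never gives the number of comparisons in the Bonferroni family, and never says whether the p < 0.05 level or the 95% interval is adjusted.

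**The concern.** There are two separate points.

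- **Sizing family.** Ten is the number of pairs among five groups. The power statement is limited to the randomised groups, of which there are four, and the analysis section lists three contrasts with control. A reader cannot tell which test the 85% refers to.
- **Decision rule for percentage change.** Bonferroni and an ordinary 95% interval are different tests of the same contrast. If the interval is unadjusted, an arm can be declared effective under one sentence and not under the other. The overall test in front of the contrasts does not repair this. It limits false positives when no arm works, but once one arm works it almost always passes and no longer protects the ineffective arms. The Discussion expects both exercise and diet to work and the combination to work best, so the case in which nothing works is not the one the investigators foresee.

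**Working it through.** **1. Counting the comparisons.** Pairs among g groups = g(g − 1)/2.

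| Family | Comparisons | Per-comparison alpha (0.05/k) |
|---|---|---|
| Three active arms versus control (Statistical methods) | 3 | 0.0167 |
| All pairs of the four randomised arms | 6 | 0.0083 |
| Stated for sizing | 10 | 0.005 |
| All pairs of the six groups, including the non-randomised references | 15 | 0.0033 |

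Ten equals 5 × 4/2, and no five-group analysis is described.

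**2. Reproducing 34 per group.** The inputs from Sample size estimation are n = 34, power 85% and alpha 0.05/10 = 0.005. Two-sided testing is assumed, as sidedness is not stated. Without a difference and SD the figure cannot be reproduced independently, so the standardised difference d was back-solved.

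- Normal approximation: d = (z for 0.005 two-sided + z for 85% power) × √(2/34) = (2.807 + 1.036) × 0.2425 = 0.932.
- Two-sample t-test (noncentral t, 66 degrees of freedom): d = 0.961.

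**3. Power at that same difference (d = 0.961, noncentral t).** With 50 per arm less 15%, 50 × 0.85 = 42.5, so about 42 remain.

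| Comparisons k | Power, 34 per arm | Power, 42 per arm |
|---|---|---|
| 3 | 93.1% | 97.3% |
| 6 | 88.9% | 95.3% |
| 10 | 85.0% | 93.2% |

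**4. Difference detectable with 85% power at 42 per arm.** For 3 contrasts it is 0.762 SD, for 5 contrasts 0.805 SD and for 10 comparisons 0.859 SD.

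**5. Familywise error for 3 contrasts with a shared control.** This was simulated with 400,000 four-arm trials per scenario, one endpoint, a one-way model and an overall F-test gate at 0.05. The one-active-arm scenario used a true effect of 0.93 SD with 50 per arm. A repeat with 0.96 SD and either 42 or 50 per arm agreed to the rounding used in the conclusion.

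| Rule, applied after the gate | No arm works | One arm works |
|---|---|---|
| 95% interval, unadjusted | 4.0% | 9.1% |
| Bonferroni over 3 | 2.9% | 3.1% |

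In the right-hand column, error counts false claims for the two ineffective arms. With one arm active the gate passed in 99.9% of trials, so the gated and ungated figures coincide there. Without the gate and with no arm working, three unadjusted intervals would give 12.5%. The plan has a gate, so that figure does not describe it.

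**The case against.** The strongest reply is that nothing in the text says the 95% interval is unadjusted. Bonferroni is named shortly before in the same analysis, and software can report Bonferroni-adjusted intervals under a 95% label, so α = 0.05 may be the familywise level. This stands: the defect is an ambiguity. A reader might infer that three different alpha levels have been fixed for one arm comparison and that error control fails. The documents do not support that. The CI sentence closes the percentage-change analysis and is not clearly attached to the intention-to-treat repeated-measures contrasts, which have their own Bonferroni rule. Even on the literal reading the gate holds error near 4% when no arm works. What is lost is control when some arms work and others do not.

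On power, the reply is that an allowance for 10 may be a cautious budget and not a count of pairs. It is also stricter than 3 or 6 contrasts require, and the trial enrols 50 per arm. This stands as well. A reader might infer that liver fat is underpowered, but at the effect implied by the plan's own figures power is higher than stated. Nor can one say that the analysis never uses 0.005, because no Bonferroni divisor is given.

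The reply does not remove the need to correct the text. Sizing refers to the randomised groups, and 10 fits no family of them that the document describes. The CI rule is a decision rule printed in the plan, and two analysts could apply it differently.

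**Conclusion.** The point holds in limited form, with moderate severity. The stated 85% power at 34 per group does not describe the 3 planned contrasts or the 6 possible pairs, but the error is on the safe side: about 93% and 89% respectively at the implied difference. These powers depend on a back-solved effect of about 0.96 SD and a two-sided two-sample t-test, because the pilot difference and SD are not given.

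The percentage-change rule is ambiguous. If the 95% interval is unadjusted, familywise error for 3 contrasts rises from about 4% when no arm works to about 9% once one arm works, against about 3% with Bonferroni over 3. If the interval is already Bonferroni-adjusted, there is no inflation and only the wording needs correcting. The error rates assume a single endpoint and equal arms.

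**What to change.** 1. Name one contrast family in Statistical methods: 3 contrasts with control, or 5 if the combination is also to be compared with exercise alone and diet alone, as the Discussion anticipates.
2. Keep the stated Bonferroni correction, give its divisor, and use the same divisor in Sample size estimation.
3. Base significance for percentage change on Bonferroni-adjusted intervals, 98.33% for 3 contrasts (1 − 0.05/3) or 99% for 5 (1 − 0.05/5), or delete the 95% CI rule.
4. Replace the statement of 10 comparisons, 34 per group and 85% with the power for the chosen family at about 42 evaluable per arm: 85% power at about 0.76 SD for 3 contrasts or 0.80 SD for 5. State the pilot difference and SD alongside it.

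The cost is wording in two sections and one recomputed power statement. No extra patients are needed.
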